## Ancillary Analysis:

a) For the quality of life study, the mean overall HRQoL score of the high risk cohort will be computed, and compared across randomized groups. Separate multivariable models will be built for the outcome of mean HRQoL score. Linear regression analysis will be performed to determine the association of a) systolic BP at baseline, b) systolic BP at follow-up; c) change in systolic BP from baseline to follow-up with and without adjusting for current use of antihypertensive medications; and b) use of antihypertensive medications. The other candidate predictors will include age, sex, level of education, and socioeconomic status.

b) For the GP survey, the means and proportions of the responses will be compared, as appropriate, for GPs in the clusters randomized to trained GP versus usual care, accounting for clustering by census. The analysis will be done per intention-to-treat as well as per-protocol (restricted to trained GP in relevant clusters).

c) For the assessment of the relationship of BP variability with LV mass and CV morbidity and mortality: BP was measured at baseline and then average of 6-monthly intervals on all high risk trial participants. All available BP readings measured at baseline and 6 monthly intervals during 2 years of intervention on high risk group will be used. We will define four metrics of BP variability based on crude systolic and diastolic BP data: 1) the standard deviation, 2) the coefficient of variation (standard deviation divided by mean BP), 3) variation independent of mean, proportional to SD/mean X, where X will be estimated for each subject by fitting a mixed-effects linear regression model of time on observed BP, which will account for greater fluctuations with higher mean BP.[50](#_ENREF_50),[67](#_ENREF_67)

We will build multivariable models for the outcomes of LVMI, E/E’ ratio and composite of CVD morbid events and all-cause mortality during 6 years. Candidate BP predictors will include BP variability, absolute baseline BP, mean of all follow-up readings, peak systolic BP achieved during any one of the visits, and episodic stage 2 systolic hypertension (systolic BP >= 160 mm Hg) during these visits. Other predictors will include age, sex, baseline BMI, tobacco use, fasting plasma glucose, and fasting blood lipids. Stepwise forward selection will be used in logistic regression time series analysis with random effects.[68](#_ENREF_68) All analyses will account for treatment assignment and clustering.

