*General Practitioner Education:* All GPs in the six study areas assigned to this intervention were invited for training, with the realistic aim to train at least two-thirds of all GPs from each area. The training of community GPs instead of specialised physicians was again to ensure a sustainable programme. The training was a one day session focused on standard treatment for the management of hypertension, based on the seventh report of the Joint National Committee (JNC 7) and the Fourth Working Party of the British Hypertension Society guidelines modified for the Indo-Asian population.[18](#_ENREF_18),[19](#_ENREF_19),[3](#_ENREF_3) Components of the course included non-pharmacological (diet, exercise, weight loss, smoking cessation) and pharmacological interventions; prescribing low cost and appropriate generic drugs; preferential use of single dose drug regimens; scheduled follow-up visits guided by level of BP; stepped care approach for titration of drugs to achieve target BP levels; and satisfactory consultation sessions for patients, with explanations of treatment and use of appropriate communication strategies.

Study Diagram

12 Clusters

n = (7,166)

Total aged 40 years and over n = (3143),

Total aged 15-39 years n = (2348),

Total aged 5-14 years n = (1675)

Household Health Education (HHE) n = (1313)

Aged 40 years and over n = (1,632),

Aged 15-39 years n = (1,175),

aged 5-14 years n = (833)

(Height, Weight, Blood Pressure, Waist Hip ratio,

Food Frequency Questionnaire, Tobacco,

Physical Activity)

Age > 40 years n = (1,511)

((FPS, lipids, ACR, ECG) ECG)

)

Ineligible for other components of the study

Age > 40 years n = (1,632)

(FPS, lipids, ACR, ECG)

Age > 40 years

with hypertension

n = 680

(FBS, lipids, ACR, ECG, Echo)

)

Usual Care

Hypertension Management

Special Care

Hypertension Management

6 Clusters

6 Clusters

Usual Care

Hypertension Management

Special Care

Hypertension Management

n = 348

n = 332

n = 326

n = 335

+ HTN

+ HTN

No HTN

No HTN

Age < 40 years

No Household Health Education (HHE) n = (1337)

Aged 40 years and over n = (1,511),

aged 15-39 years n = (1,173),

aged 5-14 years n = (842)

(Height, Weight, Blood Pressure, Waist Hip ratio,

Food Frequency Questionnaire, Tobacco,

Physical Activity)

Age > 40 years

with hypertension

n = 661

((FBS, lipids, ACR, ECG, Echo)

HTN=hypertension, FBS= fasting blood sugar, ACR= urine albumin to creatinine ratio, Echo=Echocardiography

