b) Survey of GPs for adherence to hypertension guidelines: A previous study by our group revealed serious deficiencies in knowledge and practices of GPs pertaining to hypertension treatment guidelines in Pakistan, which served as the basis for training GPs in the COBRA trial.[15](#_ENREF_15) In the latter, a total of 78 out of 110 (71%) invited GPs in the clusters assigned to trained GP intervention received the training programme. The post-test administered immediately after training session revealed significant improvement in knowledge.[3](#_ENREF_3) There were 130 GPs in the other clusters. Although we showed success of this intervention when coupled with HHE, it would be important to assess how much of the knowledge imparted during training of GPs, is retained and practised by the GPs in the long-term. This information will guide the frequency of future training sessions. Thus, we propose to conduct a survey of knowledge and practices of GPs in the communities randomized to interventions.

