## Ancillary Study- Survey of General Practitioners:

The data collectors masked to randomization status will approach all GPs practicing in the 12 randomized clusters to administer a standardized questionnaire. It will contain questions on six basic themes: a) type of practice: average number of patients seen, b) information about the GP: gender, years into practice, c) detection of high BP: whether BP is measured on all or all new patients, how many readings and when, criteria for diagnosing high BP, and whether these criteria differ for the elderly as opposed to young adults, d) evaluation of patients with high BP: whether laboratory investigations for coexisting conditions (diabetes, hyperlipidemia, kidney failure) are obtained on hypertensive patients, e) management of hypertension: patient education regarding deleterious effects of hypertension, advice on non-pharmacological measures to control hypertension, the level of BP that is targeted during treatment, and choice of antihypertensive medications, and f) types of antihypertensives used (generic or branded), g) whether antihypertensives are discontinued once BP is controlled.

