# PLAN OF ANALYSIS:

- SAS version 9.13 will be used for analyses.A p value of <0.05 will be considered statistically significant. All analyses will account for clustering at the level of census by household, as this was also the unit of randomization.[62](#_ENREF_62)

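### The GP survey's per-protocol analysis restricts only the trained side, so any difference between attenders and non-attenders is partly read as a training effect

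*Protocol*

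**What the plan says.** The survey covers every GP now working in the study areas: data collectors "will approach all GPs practicing in the 12 randomized clusters to administer a standardized questionnaire" (Protocol, Survey of General Practitioners). Responses are compared "for GPs in the clusters randomized to trained GP versus usual care, accounting for clustering by census" (Ancillary Analysis, b). Two analyses are planned: "The analysis will be done per intention-to-treat as well as per-protocol (restricted to trained GP in relevant clusters").

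On how GPs came to be trained, the Interventions section says that GPs in the six assigned areas "were invited for training, with the realistic aim to train at least two-thirds of all GPs from each area". The Rationale for ancillary studies gives the uptake: "a total of 78 out of 110 (71%) invited GPs in the clusters assigned to trained GP intervention received the training programme". It adds: "There were 130 GPs in the other clusters".

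The questionnaire records type of practice and "b) information about the GP: gender, years into practice", but Ancillary Analysis (b) does not bring these into the comparison. The general threshold is "A p value of <0.05 will be considered statistically significant", with sidedness not stated.

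**The concern.** Clusters were randomised to GP training; GPs were not. Whether an invited GP was trained was settled after allocation. The per-protocol set drops the untrained GPs from the intervention side. Their counterparts in the usual-care clusters, who would not have attended if invited, stay in the comparator and cannot be identified there. The two sides then differ in composition as well as in training, and randomisation no longer protects the contrast.

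This bears on the survey's purpose. The protocol wants to know how much of the training is still retained and practised, so as to decide how often to repeat it. Readers with that question will look at the trained-only figure. If GPs who came to the session already followed guidelines more closely than those who did not, part of the figure would be mistaken for retained knowledge. If attenders were the weaker group, a real effect would be understated.

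**Working it through.** **Stated figure.** 78/110 = 0.709, which rounds to the stated 71%. The untrained share is 32/110 = 0.291. No sample size or power is given for the survey, so there is none to reproduce.

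**Inputs from the protocol.** 78 trained of 110 invited; 130 GPs in the other clusters; 6 clusters on each side; threshold 0.05, taken as two-sided.

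**Assumed inputs, because the protocol gives none.** The attender minus non-attender gap *g* without training; a guideline item followed by about 50% of GPs (variance 0.25); ICC 0, 0.05 or 0.10; full survey response with numbers as at the trial.

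**Bias.** Let attenders score *A* and non-attenders *N* without training, and let training add *d* to attenders. Randomisation gives both sides the same expected mix.

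- Usual-care mean = 0.709*A* + 0.291*N*
- Trained-only mean = *A* + *d*
- Per-protocol contrast = *d* + 0.291(*A* − *N*) = *d* + 0.291*g*
- Intention-to-treat contrast = 0.709*d*, which is zero when *d* is zero, whatever *g* is

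With *d* = 0, gaps of 10, 20 and 30 points give 2.9, 5.8 and 8.7 points. The bias passes 5 points when *g* exceeds 5/0.291 ≈ 17 points.

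**False-positive rate with clustering.** Use cluster means, with 78/6 = 13 trained GPs and 130/6 = 21.7 usual-care GPs per cluster, and a t-test on 10 degrees of freedom. At ICC 0.05:

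- Variance of a trained-cluster mean = 0.25 × (0.05 + 0.95/13) = 0.0308
- Variance of a usual-care cluster mean = 0.25 × (0.05 + 0.95/21.7) = 0.0235
- SE of the difference = √[(0.0308 + 0.0235)/6] = 0.095, or 9.5 points

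The last row below ignores clustering: SE = √(0.25/78 + 0.25/130) = 0.072, or 7.2 points, with a normal test.

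| Rate of p < 0.05 with no training effect | gap 10 | gap 20 | gap 30 |
| --- | --- | --- | --- |
| Clustered, ICC 0.05 | 6% | 9% | 13% |
| Clustered, ICC 0.10 | 6% | 8% | 11% |
| Clustering ignored | 7% | 13% | 23% |

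**Simulation check.** A continuous score was simulated with 6 v 6 clusters, a t-test on cluster means and 6,000 runs per setting. For a gap of 0.5 SD the trained-only contrast rejected in 15% (ICC 0) and 11% (ICC 0.05) of runs. For 1.0 SD it rejected in 42% and 28%. The intention-to-treat contrast stayed between 4.7% and 5.1% throughout.

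**The case against.** The intention-to-treat analysis is already planned and is named first. The per-protocol figure is a supplement to an ancillary survey that is not in the Outcome Measures list, and selection on uptake is a familiar limit of any such analysis. The protocol also asks about retention among trained GPs, so looking at them serves its aim. All of this stands and keeps the severity low. It does not remove the bias, because the sentence itself defines a one-sided restriction and nothing else in the protocol corrects it.

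The unrestricted comparator is the plain reading of the text, not an explicit statement. Self-selection is likewise inferred from invitation and 71% uptake; no reasons for non-attendance are given.

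A reader might also infer two stronger points that the protocol does not support:

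- **That the intention-to-treat set is faulty** because it includes GPs who arrived after the training. Clusters were the unit of allocation, so counting every GP now practising there is a legitimate cluster-level comparison. Newcomers dilute it but do not create a false effect, and no turnover figure is given. Restricting to the trial's original GPs would itself condition on staying in practice, and no list of the 130 usual-care GPs is documented.
- **That the two planned estimates bracket the truth badly.** If attenders were better to begin with and training helps, intention-to-treat (0.709*d*) lies below *d* and the per-protocol contrast (*d* + 0.291*g*) lies above it, so together they do bracket the effect of being trained.

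**Conclusion.** The point holds as a low-severity improvement. As written, the trained-only contrast carries a bias of 0.291 times the attender minus non-attender gap, with the sign of that gap. It is modest unless selection was strong: 2.9 to 8.7 points for assumed gaps of 10 to 30 points. The false-positive rate is about 6% to 13% at an assumed ICC of 0.05.

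The higher rates of 7%, 13% and 23% apply only if clustering is ignored, and the protocol says that it will be accounted for. They should not be quoted as the plan's error rate. The results rest on the assumed gaps, item frequency and ICC, and on GP numbers from the trial that may have changed by the time of the survey. If attenders and non-attenders do not differ, there is no bias.

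**What to change.** In Ancillary Analysis (b):

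1. State that inference rests on the cluster-level intention-to-treat comparison of all surveyed GPs.
2. Replace the per-protocol contrast with a complier-average estimate: the intention-to-treat difference divided by the difference between arms in the proportion trained among surveyed GPs. Use small-sample cluster-level inference suited to 12 clusters. This estimate is zero when training has no effect.
3. If the trained-only comparison is kept, label it descriptive and adjust it for gender, years in practice and type of practice, all of which the questionnaire collects.

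The cost is a change of wording. Training status must be known for each surveyed GP, which the planned per-protocol analysis already requires. The complier-average estimate is less precise: its standard error is about 1/0.709 = 1.4 times that of the intention-to-treat difference, or more if turnover has lowered the proportion trained. It also assumes that training did not spill over to untrained GPs in the same clusters, which should be stated with the result.

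### The GP survey's intention-to-treat comparison is an area-level contrast of GPs now in practice; arrivals after the training dilute it as a measure of retained knowledge, and the per-protocol analysis guards against this only in part

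*Protocol*

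**What the plan says.** The protocol deals with the GP survey in four places.

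- **Purpose** (Rationale for ancillary studies, item b). The survey is to "assess how much of the knowledge imparted during training of GPs, is retained and practised by the GPs in the long-term", and then: "This information will guide the frequency of future training sessions". The same item gives the trial's GP counts: "a total of 78 out of 110 (71%) invited GPs in the clusters assigned to trained GP intervention received the training programme", and "There were 130 GPs in the other clusters".
- **Objective** (Ancillary Studies, item b). The stated objective is to evaluate the use of hypertension guidelines by practitioners in the randomised communities, which is a question about areas.
- **Who is surveyed** (Ancillary Study- Survey of General Practitioners). Masked data collectors "will approach all GPs practicing in the 12 randomized clusters to administer a standardized questionnaire". The background items listed for each GP are gender and years in practice.
- **Analysis** (Ancillary Analysis, item b). Responses are compared "for GPs in the clusters randomized to trained GP versus usual care, accounting for clustering by census". The analysis sets are given in one sentence: "The analysis will be done per intention-to-treat as well as per-protocol (restricted to trained GP in relevant clusters".

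The protocol does not define the intention-to-treat set for GPs. It gives no rule for GPs who arrived, left or moved between clusters after the training.

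**The concern.** The survey serves two questions with one frame. How GPs in these areas practise now is answered by a cross-section of everyone in practice there. Whether trained GPs kept their knowledge concerns particular people, namely those present when the training was given.

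With the open cross-section, a GP who opened a practice in a trained-GP cluster after the training is counted on the trained side without having been invited. A GP who was invited and has since left is not in the data. Calling this intention-to-treat suggests a follow-up of the GPs who were assigned, which it is not.

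The distinction matters for the use the protocol names. A weak contrast caused by turnover points to first training of newly arrived doctors. A weak contrast caused by forgetting points to more frequent retraining of the same doctors. The all-GP contrast cannot tell the two apart.

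**Working it through.** **Stated figure.** 78 of 110 invited GPs were trained: 78/110 = 70.9%, which reproduces the stated 71%. The other 110 - 78 = 32 were invited and not trained. The protocol states no sample size or power for the survey, so there is none to check.

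**Interval.** The trial ran to December 2007 (Trial in Karachi) and data collection runs from 1 April 2012 to 30 March 2013 (Data Collection), which is about 4.3 to 5.2 years after the trial's end. The Aims give 5 years after the intervention; the Background and the section on morbid and mortal events give 4. The training itself is not dated and, if given earlier in the trial, lies further back.

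**Dilution.** Let t be the share of surveyed GPs who arrived after the training. Assume that t is the same in both arms, that turnover is equal among trained and untrained GPs, that GP numbers are constant, that newcomers are untrained, and that trained GPs forget nothing. Let D be the difference between trained and untrained GPs on some item; D = 30 percentage points is illustrative.

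- Trained share in trained-GP clusters = (78/110) x (1 - t)
- All-GP difference = trained share x D

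| t (assumed) | Trained share | All-GP difference if D = 30 points |
|---|---|---|
| 0% | 70.9% | 21.3 |
| 10% | 63.8% | 19.1 |
| 20% | 56.7% | 17.0 |
| 30% | 49.6% | 14.9 |
| 40% | 42.5% | 12.8 |
| 50% | 35.5% | 10.6 |

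The all-GP difference shrinks by the factor (1 - t). In annual terms, again by assumption, 3% a year for 5 years leaves 0.97^5 = 0.86 of the original GPs and 10% a year for 7 years leaves 0.90^7 = 0.48. The trained share is then 0.709 x 0.86 = 61% or 0.709 x 0.48 = 34%. Over the interval since the trial's end, 0.97^4.3 = 0.88 and 0.90^5.2 = 0.58.

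**What the per-protocol analysis does.** Under the same assumptions it returns D = 30 at every t, so it does carry information about retention. It has three limits.

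1. The restriction is to trained GPs in the relevant clusters. Nothing restricts the usual-care arm, where newcomers stay in. If newcomers differ from long-established untrained GPs by d, the usual-care mean shifts by t x d and the trained arm's mean does not. In the all-GP comparison that shift falls on both arms.
2. It removes newcomers and the 32 invited non-attenders together. The ratio of the all-GP to the per-protocol difference is 0.709 x (1 - t): 0.71 from non-attendance alone at t = 0, and 0.50 at t = 30%. The gap between the two analyses therefore mixes non-uptake with turnover.
3. It compares GPs who chose to attend and then stayed with everyone now in the usual-care clusters, so it loses the protection of randomisation.

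**What the listed items can resolve.** Years in practice identifies recently qualified doctors. It does not identify an experienced GP who moved into the cluster, and it does not show who attended the training.

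**The case against.** A reader might infer that turnover will simply be read as lost knowledge. The documents do not support that. The sentence that names intention-to-treat also plans a per-protocol analysis restricted to trained GPs. If trained GPs had kept their knowledge while newcomers weakened the overall contrast, the two results would differ visibly. This stands, subject to the three limits shown in the working.

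A reader might also infer that the all-GP comparison is invalid. It is not. Areas were randomised, not individual GPs, and comparing current practitioners by their cluster's allocation respects the randomised unit. It also fits the objective under Ancillary Studies, item b. What remains is the label, and the use of this contrast for a retention question.

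Restricting the analysis to GPs on the original list would not restore a full intention-to-treat set either. Those still present are selected by having stayed, which happens after allocation. The protocol also gives counts, not a roster; no list of the 130 GPs in the other clusters is mentioned.

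Finally, analysis sets for an ancillary survey are commonly left to a SAP, and one may exist. That is fair for the definition of the set. It does not cover the questionnaire, because the start date in the area and attendance must be asked when the GP is interviewed. The full questionnaire is not shown, so the point rests on the themes the protocol lists.

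**Conclusion.** The point holds as a minor one. The planned comparison is a sound area-level contrast of current practice. As a measure of retained knowledge it is diluted by the factor (1 - t), and the per-protocol analysis is only a partial safeguard.

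The direction follows from the survey frame; the size is unknown. The documents give no turnover rate, so the tabulated figures and the span from 0.86 to 0.48 show sensitivity to assumed rates and are not evidence of an actual bias. They also depend on constant GP numbers, on turnover being equal between arms and between trained and untrained GPs, and on newcomers being untrained.

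The survey is ancillary. No primary or secondary outcome of the follow-up is touched.

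**What to change.** 1. Add two items to the GP questionnaire: the year the GP began practising in this area, and whether the GP attended the trial's training. Check attendance against the trial's training records where these are available.
2. Keep the all-GP comparison and label it an area-level contrast by randomised cluster.
3. Add a comparison by original cluster limited, in both arms, to GPs already practising there at the time of training. Fix the cut-off date in advance, since the protocol does not date the training and the Aims call it annual. Under the assumptions in the working, this comparison keeps the trained share at 78/110 and the expected difference at 21.3 points for any t.
4. Use that comparison together with the per-protocol result for the retention question, and state that the set is conditioned on staying.
5. Report newcomers by arm, and leavers where an original list allows.

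The cost is one or two questionnaire items, list matching, and a smaller set for the added analysis. At an assumed t of 30%, for example, 110 x 0.7 = 77 and 130 x 0.7 = 91 GPs would remain. The items must be in place before the survey starts, because they cannot be recovered from the data afterwards.

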#### Morbid and Mortal Events

Information on cardiovascular morbid events requiring hospitalization were collected at 6 monthly intervals and adjudicated by cardiologists and neurologists masked to randomization status, using guidelines recommended by the American Heart Association.[21](#_ENREF_21) Data on mortality was tracked (explained below). Deaths due to myocardial infarction, coronary revascularization, heart failure or stroke were categorized as cardiovascular deaths. During 2 years of follow-up, there were 231 composite events (cardiovascular events leading to hospitalization or all-cause mortality), 212 deaths of which 95 were due to cardiovascular causes. While the study was not powered for hard outcomes, preliminary analyses revealed an age and sex adjusted hazard ratio (95% CI) for all cause mortality for HHE versus no HHE of 0.92 (0.59-1.43), and for trained GP versus usual care GP of 0.73 (0.47-1.14). No interaction was detected between HHE and GP training on either the composite outcomes or all-cause mortality.

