## Ancillary Studies:

- a) To determine the influence of BP and antihypertensive therapy on quality of life in the high risk cohort
- b) To evaluate the use of practice guidelines for management of hypertension among practitioners in the randomized communities.
- c) To examine the relationship between BP variability during 2 years of intervention with LV mass index and cardiovascular morbidity and mortality at 7years.

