## Assessment of morbid and mortal events:

As during the main trial, all subjects aged 40 years and above in the cohort will be tracked for assessment of morbid CVD events requiring hospitalizations or death during the entire 6 years of follow-up. Since data from the initial 2 years were collected at 6 monthly intervals, relevant information during the last 4 years will be extracted from district-level official mortality registers in each cluster to track mortality. A standardized questionnaire on mortality or hospital admission during the last four years will be administered in a culturally sensitive fashion. In cases of death, the cause of death reported by the nearest family member will be recorded, and the WHO verbal autopsy questionnaire will be administered. Complete death records will be extracted, where available. However, some degree of uncertainty is expected with ascertainment of cause of death is expected in capturing mortality data on verbal autopsy from beyond the last one year. All those who report admission to hospital for a cardiovascular event, or a stroke like event will be subsequently evaluated by a study cardiologist or neurologist to confirm the diagnosis per recommendations of the American Heart Association and the European Society of Cardiology.[21](#_ENREF_21) On ethical grounds, all these patients will also be given advice regarding treatment for any complications, and prevention of future events.

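### The BP-variability analysis measures its exposures in years 0–2 but counts composite events over all six years, so early deaths make high variability and high peaks look falsely protective

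*Protocol*

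**What the plan says.** Protocol section 3.2, item c, defines the exposure window for the high-risk cohort: "All available BP readings measured at baseline and 6 monthly intervals during 2 years of intervention on high risk group will be used". The candidate BP predictors are variability, baseline BP, the mean of follow-up readings, peak systolic BP at any visit, and any visit with systolic BP of 160 mm Hg or more.

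The same item lists three outcomes: LVMI, E/E' and the "composite of CVD morbid events and all-cause mortality during 6 years". One modelling sentence follows: "Stepwise forward selection will be used in logistic regression time series analysis with random effects".

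Section 2.2 shows when the six years start. Events are tracked "during the entire 6 years of follow-up", and the two parts are then separated: "Since data from the initial 2 years were collected at 6 monthly intervals", with the remaining four years to be extracted retrospectively. The aim in section 1.6 is worded "To examine the relationship between BP variability during 2 years of intervention with LV mass index and cardiovascular morbidity and mortality at 7years", and section 1.3.5 presents the relationship as predictive.

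Section 1.2.3 reports the in-trial count: "During 2 years of follow-up, there were 231 composite events", with 212 deaths.

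**The concern.** Exposure and outcome share the first two years. Someone who dies in month 8 is an event, but has at most two BP visits. Someone who survives the window can have five. SD from few readings is biased low, the maximum of few readings is lower, and there are fewer chances of crossing 160. The number of readings therefore depends on the outcome, and these metrics depend on the number of readings.

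The result is an association between low variability or low peak and the composite even where none exists. A true harmful association would be pulled towards or past the null. Readings taken after a non-fatal event may also reflect that event or its treatment. The documents do not allow the direction of that second effect to be stated.

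A separate and lesser matter is that the only model named does not suit two of the three outcomes, and that forward selection is to run over BP metrics all derived from the same readings.

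**Working it through.** The protocol gives no sample size or power figure for this analysis, so there is nothing of its own to reproduce.

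**1. Windows.** Exposure: years 0–2 (section 3.2). Composite: six years (section 3.2). Section 2.2: 2 initial + 4 later = 6. The exposure window lies wholly inside the outcome window. Item c states no landmark, exclusion of early events or time-updated exposure.

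**2. Share of events inside the exposure window.** Inputs: 231 composite events in two years (section 1.2.3). No denominator is given there, so take 1,341 hypertensives (section 1.2.3; 332 + 348 + 335 + 326 = 1,341) and all 3,143 aged 40 and over (study diagram, section 1.2.2). Assume a constant hazard h.

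- h = −ln(1 − 231/N)/2, which is 0.0945 per year for N = 1,341 (17.2% in two years) and 0.0382 for N = 3,143 (7.3%).
- Share = (1 − e^(−2h))/(1 − e^(−6h)).
- N = 1,341: 0.1723/0.4329 = 0.398. N = 3,143: 0.0735/0.2047 = 0.359.

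Section 1.6 speaks of seven years. With 7h in the denominator the shares are 0.1723/0.4840 = 0.356 and 0.0735/0.2345 = 0.313.

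**3. Why fewer visits lower the SD.** For n independent normal readings, E(SD) = c4(n)·σ, with c4(2) = 0.798, c4(3) = 0.886 and c4(5) = 0.940. Two visits against five: 0.798/0.940 = 0.85, so 15% lower. Three against five: 0.886/0.940 = 0.94, so 6% lower. Similarly, if each visit has chance p of a reading of 160 or more, the chance of at least one is 1 − (1 − p)^n, which rises with n.

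**4. Size of the effect when nothing is there.** Null simulation with 400 replicates of 1,341 people, BP unrelated to events. Assumptions not in the documents: mean SBP 150, between-person SD 15, within-person SD 8, 12 or 16 mm Hg, no time trend, one value per visit at 0, 6, 12, 18 and 24 months, every event ends the BP series, and at least two readings are needed. The model is ordinary logistic regression of the event by six years on one metric plus mean BP. Ranges cover both event rates and all three within-person SDs; the true odds ratio is 1.

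| Metric | OR, plan as written | False-positive rate at 0.05 | OR with 2-year landmark |
| --- | --- | --- | --- |
| SD, per 5 mm Hg | 0.89–0.94 | 16–23% | 0.99–1.01 |
| Peak SBP, per 10 mm Hg | 0.56–0.76 | 80% to over 99% | 0.99–1.00 |
| Any SBP of 160 or more | 0.70–0.82 | 13–57% | 0.99–1.01 |

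With the landmark, false-positive rates were about 3–6% for all three metrics. Monte Carlo error moves the limits of the odds ratios by about 0.01.

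**5. Outcomes to which this does not apply.** LVMI and E/E' come from one echocardiogram at post-trial follow-up (sections 2.1 and 2.4), after the exposure window has closed. Only people who lived to be scanned contribute, so early deaths cannot enter as outcomes. What remains is survivor selection, which is a different matter.

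**6. Model named.** LVMI is in grams per square metre (section 2.1) and E/E' is a ratio. Item c gives no cut-off for either, whereas item a of the same section names linear regression for the quality-of-life score.

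**The case against.** The overlap itself is hard to dispute. The objections limit how far it reaches.

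- **A reader might infer that the whole analysis is biased and that no predictive claim is possible.** That goes too far. The echo outcomes are outside the overlap, and no randomised comparison in section 3.1 depends on item c.
- **A reader might infer that the plan applies logistic regression to continuous LVMI and E/E'.** It does not say so. It lists three outcomes and names one model, without assigning it, and a SAP not shown may settle this. The diastolic-dysfunction grades in section 2.1 could also be modelled as categories. What stands is that the one model named does not fit these two outcomes as they are listed. This is an unclear specification, not a bias.
- **A reader might fault the third variability metric,** "where X will be estimated for each subject by fitting a mixed-effects linear regression model of time on observed BP". The formula is damaged in the text and rests on cited sources not at hand, and a mixed-effects model is fitted across subjects in any case. The documents do not support a finding here.
- **The 231 events may not all belong to the high-risk cohort.** This is correct, and it is why both denominators are used.
- **The 15% deficit in SD is the extreme case, and section 1.3.5 describes two readings per visit.** Both are fair. The size depends on how many readings people have and how they are combined; the mechanism does not.
- **Not every event ends the BP series.** True, but 212 deaths against 231 composite events in two years means deaths dominate.
- **The analysis is ancillary and described as exploratory.** This limits the consequence. It does not make the estimate right.

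**Conclusion.** The point holds for the composite outcome. Followed as written, item c relates metrics from years 0–2 to events that partly occur in years 0–2, and early death shortens the exposure record. The truncation pushes the odds ratios for SD, peak SBP and any reading of 160 or more below 1 when the truth is 1. Peak SBP is hit hardest.

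About 36–40% of six-year first events fall in the exposure window if the hazard is constant. The simulated odds ratios rest on the assumed BP distribution and on events ending the BP series. They cover truncation only, not BP changes after a non-fatal event. The simulated model is also simpler than the random-effects model the plan names.

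The consequence is confined to one ancillary, non-randomised analysis. The unclear model for LVMI and E/E' and the forward selection are secondary. Selecting among overlapping BP metrics tends to give over-optimistic estimates and p-values, but no size has been put on that here.

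**What to change.** For the composite in item c, set a landmark at 24 months. Include only participants alive and free of a composite event then, compute the BP metrics from readings up to that point, and count only later events. Time-updated BP metrics in a time-to-event model are an alternative. Logistic regression with the landmark was enough to restore the null in the simulation, so Cox regression or a minimum number of visits is optional. State whether follow-up ends at six or seven years, since sections 1.6 and 3.2 differ.

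Secondary changes: state linear mixed models for LVMI and E/E'. Replace forward selection with a fixed covariate set taken from the predictors already listed, adding one BP metric at a time. Keep treatment assignment and clustering in all models, as the plan already says.

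Cost: protocol text only, with no new data. The price is that first-two-year events leave this analysis. In the simulated cohort the events analysed fell from about 520 to 350 at the higher event rate and from about 249 to 176 at the lower. The lost events cannot support a predictive claim in any case.
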